### **Primary Outcome**

#### **Saturated Fat Intake**

a) Self-reported amount of saturated fat intake will be measured by Margetts et al (1989) 63 item food frequency questionnaire and a two-item self-reported measure. The Margetts, Cade & Osmond (1989) questionnaire is a validated self-report index of food. The frequency of consumption of 63 common foods over the previous month using a 6-point-scale is assessed (two or more times per day; three to five times per week; one to three times per month; rarely or never). The scale has good test-retest reliability ( $r=.61$ ; Armitage & Conner, 1999). In this study a column on reduction on portion sizes will be added and assessed at Time2.

b) Saturated fat intake will be also measured by a two item self perception questionnaire.

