## **11. Statistical Considerations**

### **11.1 Description of Statistical methods and interim analysis**

This is a randomised, stratified, between-groups study with the factors 'Planning' and 'SMS Reminders'. The primary endpoint is the change in saturated fat and portion size changes in participants allocated to the three different experimental conditions (Planning, Planning and SMS Reminders and Control Group). Participants will be randomly allocated to one of these three conditions, stratifying for age group (30-45 years or 46-60 years) and gender. Self-reported portion size changes will be measured at a single point at the end of the study. Participants' saturated fat intake will be measured at baseline and upon completion of the study (2 weeks after enrolment). The statistical analysis will compare the efficacy of the three treatment groups via the change in saturated fat intake between the baseline and final diet assessments and change in portion sizes at the end of the study. There will be no interim analyses.

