## APPENDIX 3 – QUESTIONNAIRES

Self-Report Index of Food (Margetts et al, 1989): Stage 1/2

This questionnaire will be presented to subjects with the title 'Eating Habits'

Please choose the frequency with which you have eaten each of the foods in the list below.

| Food                        | 2 or more times per day | Every day | Three to five times per week | One to two times per week | One to three times per month | Rarely or never |
|-----------------------------|-------------------------|-----------|------------------------------|---------------------------|------------------------------|-----------------|
| Whole milk                  |                         |           |                              |                           |                              |                 |
| Semi-skimmed milk           |                         |           |                              |                           |                              |                 |
| Skimmed milk                |                         |           |                              |                           |                              |                 |
| Butter                      |                         |           |                              |                           |                              |                 |
| Margarine                   |                         |           |                              |                           |                              |                 |
| Polyunsaturated margarine   |                         |           |                              |                           |                              |                 |
| Low fat spread              |                         |           |                              |                           |                              |                 |
| Ice cream                   |                         |           |                              |                           |                              |                 |
| Yoghurt                     |                         |           |                              |                           |                              |                 |
| Cheese- ordinary            |                         |           |                              |                           |                              |                 |

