#### Portion Changes: Stage2

This question will be presented to subjects with the title 'Portion Changes'

During the last 4 weeks, my portions of the foods below were:

| A lot smaller             | A lot bigger |   |   |   |   |   |   |
|---------------------------|--------------|---|---|---|---|---|---|
|                           | 1            | 2 | 3 | 4 | 5 | 6 | 7 |
| Meat dishes               |              |   |   |   |   |   |   |
| Cheese ordinary           |              |   |   |   |   |   |   |
| Cheese/egg meals          |              |   |   |   |   |   |   |
| Butter                    |              |   |   |   |   |   |   |
| Whole Milk                |              |   |   |   |   |   |   |
| Bacon                     |              |   |   |   |   |   |   |
| Beef- roast/steak         |              |   |   |   |   |   |   |
| Pork-roast/chops          |              |   |   |   |   |   |   |
| Lamb-roast/chops          |              |   |   |   |   |   |   |
| Chocolate                 |              |   |   |   |   |   |   |
| Crisps and savoury snacks |              |   |   |   |   |   |   |

### Perceptions of saturated fat intake: Stage 1/ 2

These two questions will be presented to subjects with the title 'Eating Habits'

|                                                            |                   |                |   |   |   |   |   |  |
|------------------------------------------------------------|-------------------|----------------|---|---|---|---|---|--|
|                                                            | Strongly Disagree | Strongly Agree |   |   |   |   |   |  |
| I have eaten foods high in bad fats in the last four weeks | 1                 | 2              | 3 | 4 | 5 | 6 | 7 |  |

|                                                                      |       |            |   |   |   |   |   |  |
|----------------------------------------------------------------------|-------|------------|---|---|---|---|---|--|
|                                                                      | Never | Frequently |   |   |   |   |   |  |
| How often did you eat foods high in bad fats in the last four weeks? | 1     | 2          | 3 | 4 | 5 | 6 | 7 |  |

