## Intentions: Stage 1/2

This question will be presented to subjects with the title 'Dietary Beliefs'

Please rate your intentions to change the following aspects of your diet over the next two weeks.

Over the next four weeks I intend to....

|                                              | Strongly
1 | Strongly
2 | Disagree
3 | 4 | 5 | Agree
6 | 7 |
|----------------------------------------------|---------------|---------------|---------------|---|---|------------|---|
| Replace high fat with lower fat alternatives |               |               |               |   |   |            |   |
| Eat smaller portions of high fat foods       |               |               |               |   |   |            |   |
| Reduce the amount of bad fats in my diet     |               |               |               |   |   |            |   |

## General Health Behaviours: Stage 2

This question will be presented to subjects with the title 'Your General Health Behaviours'

Compared to usual, over the last four weeks did you.....

|                                   | A lot
less
1 | About the
Same
2 | A lot
more
3 | 4 | 5 | 6 | 7 |
|-----------------------------------|--------------------|------------------------|--------------------|---|---|---|---|
| Drink alcohol                     |                    |                        |                    |   |   |   |   |
| Use Cholesterol lowering products |                    |                        |                    |   |   |   |   |
| Find you weigh                    |                    |                        |                    |   |   |   |   |

|                           |  |  |  |  |  |  |  |
|---------------------------|--|--|--|--|--|--|--|
| Smoke                     |  |  |  |  |  |  |  |
| Take up physical activity |  |  |  |  |  |  |  |
| Eat a well-balanced diet  |  |  |  |  |  |  |  |
| Choose lower fat foods    |  |  |  |  |  |  |  |

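### The food frequency form gives subjects no recall period, although Protocol section 5.2 defines the measure over the previous month

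*Protocol*

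**What the plan says.** Section 5.2 lists the FFQ under the primary outcome: "Self-reported amount of saturated fat intake will be measured by Margetts et al (1989) 63 item food frequency questionnaire and a two-item self-reported measure". It defines the period covered: "The frequency of consumption of 63 common foods over the previous month using a 6-point-scale is assessed".

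Appendix 3 reproduces the form under the label "Self-Report Index of Food (Margetts et al, 1989): Stage 1/2", so the same form serves baseline and follow-up. Its whole instruction to the subject is "Please choose the frequency with which you have eaten each of the foods in the list below".

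The other retrospective forms in Appendix 3 each state a window:

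- Portion changes: "During the last 4 weeks, my portions of the foods below were".
- Two-item fat measure: "How often did you eat foods high in bad fats in the last four weeks". Its companion item names the same period.
- General health behaviours: "Compared to usual, over the last four weeks did you".

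Section 11.1 compares the arms on change in saturated fat intake from baseline to the final assessment. It places that assessment "upon completion of the study (2 weeks after enrolment"). The Protocol Summary and section 1.3 put Time 2 four weeks after Time 1.

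**The concern.** The subject answers the form, not section 5.2. Without a stated period, each subject chooses one, and different subjects may choose different ones.

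At baseline this does little harm to the comparison of arms, because every period a subject might choose lies before the intervention. At Time 2 it can matter. A subject who thinks back further than the follow-up interval mixes pre-intervention weeks into the answer. Randomised arms should not differ in those weeks, so mixing them in moves the difference between arms towards zero.

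Section 1.2 reports that saturated fat effects in the sponsor's previous study were small, and it gives the need for better measures as one reason for the present trial. Avoidable loss of sensitivity in a primary instrument is therefore unwelcome. The wording determines what data are collected, so no later analysis can recover the intended window.

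**Working it through.** **1. Is the omission real, or lost in text extraction?** The form's label, title, instruction and six column headings are all present. Counting the foods in successive blocks of the table gives 10 + 14 + 14 + 5 + 9 + 11 = 63, the number stated in section 5.2. Nothing suggests a missing line. One column counts occasions per month, but that is a unit of frequency and does not say which month is meant.

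**2. Forms side by side.**

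| Form (Appendix 3) | Stage | Period stated to the subject |
|---|---|---|
| FFQ | 1 and 2 | none |
| Two-item fat measure | 1 and 2 | last four weeks |
| Portion changes | 2 | last four weeks |
| General health behaviours | 2 | last four weeks |

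The FFQ is the only retrospective intake or behaviour form without a window.

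**3. The plan's own sample size figure.** Section 11.3 says that around 180 respondents give power 0.8 at the two-sided 0.05 level for control against planning. It gives no effect size or standard deviation and does not say whether 180 is per arm or in total, so the figure cannot be reproduced. The standardised effect it implies follows from d = (1.960 + 0.842) × √(2/n):

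- 180 per arm: d = 2.802 × √(2/180) = 0.295.
- 180 in total, 90 per arm: d = 2.802 × √(2/90) = 0.418.

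**4. Completers.** Section 6.2 expects roughly 500 subjects at Time 2 after 30% drop-out (725 × 0.7 = 507.5). Equal allocation is assumed, giving 500/3 ≈ 167 per arm.

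**5. Illustration of dilution.** Let f be the share of the Time 2 answer that describes pre-intervention diet. The documents give no value for f, so a range is shown. If the standard deviation stays fixed, the effective effect is d(1 − f), and power ≈ Φ(d(1 − f)√(n/2) − 1.960) with n = 500/3:

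| f | Power, d = 0.295 | Power, d = 0.418 |
|---|---|---|
| 0 | 0.77 | 0.97 |
| 0.10 | 0.68 | 0.93 |
| 0.25 | 0.525 | 0.82 |
| 0.50 | 0.27 | 0.48 |

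**6. Why these are lower bounds.** Suppose the Time 2 answer is f × pre + (1 − f) × post. Subtracting the baseline value leaves (1 − f)(post − pre), so true change shrinks in both mean and standard deviation. Only independent reporting error keeps its size. If r is the share of residual variance due to reporting error, the effective effect is d(1 − f)/√(r + (1 − r)(1 − f)²). At f = 0.5 and d = 0.295:

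- r = 1: 0.295 × 0.5/1 = 0.148, power 0.27.
- r = 0.5: 0.295 × 0.5/√(0.5 + 0.5 × 0.25) = 0.187, power 0.40.
- r = 0: 0.295, power 0.77, no loss.

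**7. Timing.** A four-week window asked at four weeks lies wholly after the intervention. Asked at two weeks, 2/4 = one half of it lies before. That follows from the visit date and would remain with a corrected stem.

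**The case against.** The strongest reply is that section 5.2 already fixes the intended window, the appendix stem was simply not matched to it, and any dilution is conjecture. Several parts of this stand.

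- A reader might infer from the form's on-screen title, which speaks of habits, that subjects will describe their usual diet. The documents do not support this. The two-item fat measure carries the same title and states four weeks.
- A reader might take the power figures as the loss facing the primary analysis. They are not. Section 11.3 powers self-perceived saturated fat reduction. That wording fits the two-item measure better, since section 5.2 calls it a self-perception questionnaire, and that measure already has its window. Applying its implied effect to the FFQ is a borrowing made only to show sensitivity.
- A reader might treat the FFQ as the one primary instrument. Sections 2.1 and 5.2 list it beside the two-item and portion-size measures without ranking them, and those two state their period.
- A reader might count the two-week statement in section 11.1 as part of this defect. It is a separate inconsistency, and correcting the stem would not resolve it.

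What the reply does not remove is the mismatch itself. The intended window is in the body of the protocol, where subjects will not see it.

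**Conclusion.** The point holds as a contradiction between section 5.2 and the form in Appendix 3, and this needs no calculation. The consequence is a possible loss of sensitivity in one of several primary measures. Its direction is towards no difference between arms, and its size cannot be derived from the documents.

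The fall in power at f = 0.5, to 0.27 or 0.48 according to how the 180 is read, is a worst case. It assumes that half of the Time 2 answer is pre-intervention diet, that all residual variance is reporting error, that allocation is equal with 167 completers per arm, and that the effect behind the 180 applies to the FFQ. None of these is stated in the protocol. The change should be made because it costs almost nothing beforehand and cannot be made after data collection. The documents do not show that the trial would fail without it.

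**What to change.** In Appendix 3, at both stages, change the FFQ stem to: 'Over the last four weeks, how often have you eaten each of the foods below?' This matches the sister forms. Section 5.2 can take the same wording so that text and form agree. The cost is one sentence on an online form and a matching edit to the protocol, with no added burden on subjects.

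Separately, reconcile the assessment point in section 11.1 with the four weeks given in the Protocol Summary and section 1.3. The four-week window lies wholly after the intervention only if Time 2 is at least four weeks after Time 1. The cost is one correction to the text.

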#### Portion Changes: Stage2

This question will be presented to subjects with the title 'Portion Changes'

During the last 4 weeks, my portions of the foods below were:

| A lot smaller             | A lot bigger |   |   |   |   |   |   |
|---------------------------|--------------|---|---|---|---|---|---|
|                           | 1            | 2 | 3 | 4 | 5 | 6 | 7 |
| Meat dishes               |              |   |   |   |   |   |   |
| Cheese ordinary           |              |   |   |   |   |   |   |
| Cheese/egg meals          |              |   |   |   |   |   |   |
| Butter                    |              |   |   |   |   |   |   |
| Whole Milk                |              |   |   |   |   |   |   |
| Bacon                     |              |   |   |   |   |   |   |
| Beef- roast/steak         |              |   |   |   |   |   |   |
| Pork-roast/chops          |              |   |   |   |   |   |   |
| Lamb-roast/chops          |              |   |   |   |   |   |   |
| Chocolate                 |              |   |   |   |   |   |   |
| Crisps and savoury snacks |              |   |   |   |   |   |   |

### Perceptions of saturated fat intake: Stage 1/ 2

These two questions will be presented to subjects with the title 'Eating Habits'

|                                                            |                   |                |   |   |   |   |   |  |
|------------------------------------------------------------|-------------------|----------------|---|---|---|---|---|--|
|                                                            | Strongly Disagree | Strongly Agree |   |   |   |   |   |  |
| I have eaten foods high in bad fats in the last four weeks | 1                 | 2              | 3 | 4 | 5 | 6 | 7 |  |

|                                                                      |       |            |   |   |   |   |   |  |
|----------------------------------------------------------------------|-------|------------|---|---|---|---|---|--|
|                                                                      | Never | Frequently |   |   |   |   |   |  |
| How often did you eat foods high in bad fats in the last four weeks? | 1     | 2          | 3 | 4 | 5 | 6 | 7 |  |

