#### **c) Portion Size Changes**

Portion size changes in the consumption of 11 high fat items (e.g. meat dishes, whole milk, bacon, cheese ordinary, chocolate, crisps) will be assessed. These items accounted for the highest reported saturated fat intake in the FFQ from a previous study. Participants will be asked to report changes in their portion sizes on a 7 point Likert scale (from 'a lot less' to 'a lot more').

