## **7. Investigational Events**

### **7.1 Endpoints**

#### **7.1.1 Primary**

The primary endpoint is:

- a) Self-Reported Saturated Fat Intake
- b) Portion Size Changes

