**Don't go for things that you are already doing**

[figure not shown]

### Slide 2

In this page you will set your **THREE PLANS**. Please follow instructions in the bubbles. It might take a few seconds for the system to load each selection. There are no right or wrong choices!

| Situations                             |  | Solutions                                               |
|----------------------------------------|--|---------------------------------------------------------|
| If I go shopping                       |  | Then I will choose a lower fat spread                   |
| If I go for a dish with cheese         |  | Then I will choose a low fat dairy product              |
| If I'm getting a snack                 |  | Then I will go for chicken                              |
| If I'm having lunch/dinner             |  | Then I will find out about a lower fat option           |
| If I'm having breakfast                |  | Then I will go for oily fish                            |
| If I'm in a restaurant                 |  | Then I will go for fruit instead of chocolate/crisps    |
| If I'm having a good time with friends |  | Then I will not buy high fat foods to keep in the house |
| If I'm feeling down or upset           |  | Then I will tell myself I can eat healthy!              |
| If I'm craving a high fat food         |  | Then I will find something to distract myself           |
| If I'm feeling hungry                  |  | Then I will choose a lower fat cheese with it           |
| If I had a hard day                    |  | Then I will go for a smaller portion of the same food   |

|                                               |  |                                                 |
|-----------------------------------------------|--|-------------------------------------------------|
| If others around me are eating high-fat foods |  | Then I will go for a vegetable dish or soup     |
| If I want to have a lamb or pork dish         |  | Then I will distract myself with something else |

### Slide 3

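### The portion-change form, a primary endpoint, has no answer for a food not eaten, so a 4 or a 1 can mean different things, probably more often in the planning arms

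*Protocol*

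**What the plan says.** Protocol 7.1.1 lists "Portion Size Changes" as primary endpoint (b). Section 11.1 fixes the timing: "Self-reported portion size changes will be measured at a single point at the end of the study". Section 5.2(c) describes "Portion size changes in the consumption of 11 high fat items" and adds: "Participants will be asked to report changes in their portion sizes on a 7 point Likert scale". The foods were chosen from an earlier sample: "These items accounted for the highest reported saturated fat intake in the FFQ from a previous study".

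The printed form (Appendix 3, Portion Changes) opens with "During the last 4 weeks, my portions of the foods below were" and gives each food columns 1 to 7, from much smaller to much bigger. There is no other column, and no section says how a food that was not eaten is to be answered or scored. The food frequency questionnaire (FFQ) in the same appendix, given at both stages, does have such a category: "Rarely or never".

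The Appendix 4 plans include "Then I will choose a lower fat spread", fruit in place of chocolate or crisps, and not buying high-fat foods for the house. The Slide 3 reminder advises avoiding roasts and chops, among other meats. One plan is a smaller portion of the same food.

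**The concern.** The question presumes that every food was eaten. A person who never uses whole milk or never eats bacon has no portion to rate. A person who gave up a food during the four weeks has made the largest possible cut, but the form does not say where to record it. A 4 may therefore mean an unchanged portion, a food never eaten, or a food given up. A 1 may mean a much smaller portion, none now, or none ever.

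Two effects follow. Varied answers from never-eaters add between-person noise in every arm. Stoppers who tick the mid-point remove a real reduction from the score, and do so more in whichever arm has more stoppers. Since the planning material encourages avoidance and substitution, that is likely to be the planning arms. The form has no baseline, and once Time 2 data are in, the meaning of a 4 cannot be recovered from the form.

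**Working it through.** **No figure to reproduce.** Section 11.3 states that no prior data exist for this measure. The only size input from the protocol is roughly 500 subjects at Time 2 (section 6.2; 725 × 0.70 = 507.5 agrees), or 500/3 ≈ 167 per arm with equal allocation. Every other input below is an assumption.

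**1. Form against planning material.** Beef, pork and lamb (roast, chops or steak) are three of the 11 rows and fall under the Slide 3 avoidance advice. Chocolate and crisps are two more, covered by the fruit substitution. The spread and dairy plans bear on butter, whole milk and ordinary cheese without naming butter or whole milk as foods to give up. All 11 foods also appear on the FFQ.

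**2. Stoppers, one food.** Assume eaters average 4.0 in control and 3.7 in planning, 2% of controls stop, a share *s* of the planning arm stops, and stoppers tick *t*.

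Control mean = 0.98 × 4 + 0.02*t*; planning mean = (1 − *s*) × 3.7 + *s* *t*.

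| *s* | *t* | Control | Planning | Difference |
|---|---|---|---|---|
| 0.10 | 1 | 3.94 | 3.43 | 0.51 |
| 0.10 | 4 | 4.00 | 3.73 | 0.27 |
| 0.20 | 1 | 3.94 | 3.16 | 0.78 |
| 0.20 | 4 | 4.00 | 3.76 | 0.24 |

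The undefined answer changes the difference by a factor of 0.51/0.27 ≈ 1.9 to 0.78/0.24 ≈ 3.3. With 2% stopping in both arms the difference is 0.294 whichever answer is ticked, so this effect depends on stopping differing by arm.

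**3. Never-eaters, one food.** Power = Φ(δ / (σ√(2/n)) − 1.96), with √(2/167) = 0.1094, and δ = 0.30 and σ = 1 among eaters. If everyone eats the food, power is 78%. Now let 20% never eat it.

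- All tick 4: δ = 0.8 × 0.30 = 0.24 and σ ≈ √0.8 = 0.894, so power is 69%.
- Their rows are left out: n = 0.8 × 167 = 133.6, δ = 0.30, σ = 1, power 69%. A uniform mid-point answer therefore shrinks the difference but costs no power against leaving the rows out.
- Half tick 1 and half tick 4: the means are 3.70 and 3.46, so δ = 0.24. Control variance = 0.8(1 + 0.3²) + 0.1(0.3²) + 0.1(2.7²) = 1.61. Planning variance = 0.8(1 + 0.24²) + 0.1(0.54²) + 0.1(2.46²) = 1.48. Then σ = √1.545 = 1.243, and power = Φ(0.24/0.136 − 1.96) = 42%.

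**4. Simulated mean of the 11 items.** Assumed: 167 per arm, 27% of rows never eaten, a shift of 0.15 per eaten row, person SD 0.6, item SD between 0.6 and 1.3, two-sample t test. The comparator has a not-eaten box, never-eaten rows left out and stopped rows scored 1.

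| Rows stopped, planning v control | With box | Form as printed |
|---|---|---|
| 3% v 3% | 0.41–0.52 | no loss if all tick 4; 0.24–0.30 if half tick 1 and half tick 4 |
| 6% v 3% | 0.77–0.85 | 0.34–0.52 (mid-point or half-and-half) |
| 10% v 3% | about 0.99 | 0.99–1.00 if never-eaters tick 4 and stoppers tick 1; 0.35–0.63 if mid-point or half-and-half |

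The high values in the box column arise partly because stopping is itself scored as the largest reduction.

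**5. A scoring rule can also do harm.** If 15% of eaten rows are missed by chance in the four weeks and every newly uneaten food scores 1, power was 0.36 with the box against 0.42–0.43 with the printed form (3% stopping in both arms, item SD 1.0).

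**The case against.** The most natural reading of the form may be harmless: a never-eater ticks 4 for no change and a stopper ticks 1. On that pattern nothing is lost. This stands, and it is why the size cannot be stated as a single figure.

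The FFQ covers the same 11 foods at both stages, so a later analysis plan could flag never-eaters and stoppers without changing the form. This stands in part. The lowest FFQ category merges rare eaters with non-eaters, so it identifies stoppers only approximately.

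Frequency change is captured by the other primary endpoint, saturated fat intake. That limits the harm to the trial as a whole but does not repair this endpoint.

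A reader might infer that the planning arms are told to stop these foods, that subjects must tick a score, and that the bias falls in those arms alone. The documents do not support this. The plans are self-chosen and tied to situations, one is a smaller portion, and the avoidance advice covers only some of the foods. Mandatory answering is not stated, although section 9.4 says withheld information may prevent completion. Controls may stop foods too: section 1.3 gives all groups the educational material, which suggests switching from butter, while section 5.1 gives it to controls only at the end.

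**Conclusion.** The point holds as a gap in the instrument for a primary endpoint: the printed form has no defined answer for a food that was not eaten, and nothing else in the protocol supplies one. That giving up a food will be commoner in the planning arms is a reasonable expectation from Appendix 4, not a stated fact. The direction follows if stoppers tick the mid-point: the portion effect moves towards zero. The size is unknown. Under the assumptions above it runs from no loss to more than half the power (for example 0.99 to 0.35). Those figures also assume that the score is the mean of the 11 items, which the protocol does not state. This is a cheap improvement worth making before Time 2, not a flaw that invalidates the endpoint.

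**What to change.** Add an answer such as 'I did not eat this food in the last 4 weeks' to each row, and fix its scoring before any data are seen, using the same food's Stage 1 FFQ row:

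- In the lowest FFQ category at Stage 1: leave the row out of the subject's mean.
- Eaten at least weekly at Stage 1: score the row as the largest reduction (1).
- Eaten less than weekly at Stage 1: leave the row out, so that a chance gap in an occasional food is not counted as a reduction.

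Report a sensitivity analysis that leaves out all not-eaten rows.

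The cost is one extra column online and one scoring rule. Subjects who eat few of the foods contribute fewer rows, and genuine stopping of an occasional food is not credited. Rows left out because of a Stage 2 answer are selected after randomisation, so the number left out should be reported by arm. The weekly threshold was not simulated. It credits fewer stopped rows than the comparator in the working, so its gain would be smaller than shown there when there are no chance gaps.
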